**Methods:**

A 2 × 2 factorial, single blind RCT with immediate, short- and long-term follow-ups. One hundred and sixty eight participants with neck pain with impaired joint position sense and balance will be recruited into the trial. Participants will be randomly allocated to one of four intervention groups: i) local neck treatment, ii) local treatment plus tailored sensorimotor exercises, iii) local treatment plus balance exercises, and iv) local treatment plus sensorimotor and balance exercises. Participants receive two treatments for 6 weeks. Primary outcomes are postural sway and cervical joint position error. Secondary outcomes include gait speed, dizziness intensity, neck pain intensity, neck disability, pain extent and location, cervical range of motion, functional ability, perceived benefit, and quality of life. Assessment will be measured at baseline, immediately after treatment and at 3, 6, 12 month-follow ups.

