### Outcome measures (Table 5)

#### Primary outcomes

##### Postural stability

A sway meter will be used to measure the extent of postural sway and displacement. The sway meter is a simple tool for assessing postural sway in individuals with impaired balance [38]. It has been shown to have good test-retest reliability (ICCs = 0.65-0.94) and good validity (r with forceplate = 0.56-0.87) [38]. The sway meter consists of a 40 cm long rod with a vertically mounted pen at its end. It will be firmly attached to the participant’s waist using a webbing strap. During the test, the pen will record participant’s sway on a millimeter graph paper fastened to the top of an adjustable-height table. Maximum displacement in anterior-posterior (APmax) and medial-lateral (MLmax) directions and total sway (number of square millimeter squares traversed by the pen) will be recorded. The postural sway will be measured in 8 conditions as follows: narrow stance (feet close together) on firm and soft surfaces with eyes open and eyes closed [39] and during a neck torsion maneuver (head turned 45° to the left and right) on firm and soft surfaces [40]. Participants will be tested barefoot and asked to stand still without talking for 30s for each condition. Participants are allowed a maximum of two additional attempts if they are unable to maintain the position for 30s. A rest period of 60s will be given between each condition.

**Table 5 Tab5:** Summary of outcome measures

Primary outcome measures	Data collection instruments
Postural stability	A swaymeter
- Sway displacement	
- Sway area	
Cervical joint position error	A laser-pointer attached to a lightweight headband
Secondary outcome measures	
Gait speed	10-m walk test
Dizziness intensity	VAS (0-100 mm)
Neck pain intensity	VAS (0-100 mm)
Neck disability	NDI-TH (0-100)
Pain extent and location	iPad and custom software
Cervical range of motion	A CROM instrument
Functional ability status	PFSF (scale range 0-10)
Health-related quality of life	Thai SF-36 (scale range 0-100)
Global perceived benefit of treatment	A seven-point ordinal Likert scale (1-7)

All outcome measures will be recorded at baseline, immediately after intervention, 3, 6 and 12 months follow-ups. *VAS* Visual analogue scale, *NDI-TH* Neck disability index-Thai version, *Thai SF-36* Thai version of short form 36, *CROM* Cervical range of motion, *PFSF* The patient-specific functional scale

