### Sample size

The sample size estimates are calculated based on the primary outcomes (postural stability and cervical JPE) from baseline to follow-ups. According to our previous data, we consider a sample size that gives 80% power with a 5% confidence level to detect a significant difference of 21.9 cm^2^ (SD = 12.3) for postural sway and 4.5° (SD = 3.2) for JPE. Sample size estimates were performed using both two-way ANOVA and repeated measure ANOVA (two-tailed) and the optimum number of 35 participants per group is required. To allow for 20% drop out rate, a total sample size of 168 participants (42 per group) will be recruited for this trial.

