### Statistical analysis

SPSS version 17.0 or higher will be used for statistical analysis. Descriptive statistics will be used to describe demographic data and baseline characteristics and follow-ups for each treatment group. Two-way mixed ANOVA will be used to determine within-subject and between subject variables. Main effects for independent variables (local treatment/sensorimotor exercise and local treatment/balance exercise) and the intervention effects of the independent variables immediately after treatment and at 3, 6 and 12 month follow-ups will be analyzed. This allows the individual effects of sensorimotor exercise and balance exercise to be examined as well as whether there will be an additive effect of applying both sensorimotor and balance exercises in a multimodal treatment. Differences in mean change (baseline minus follow-up) will be compared between groups using baseline values of the outcomes as covariates.

Effect sizes will be calculated by taking the difference in mean changes in the primary outcomes between the intervention groups and control group (local neck treatment alone). An effect size of 0.2 will be regarded as small, 0.5 as medium and 0.8 as large [55]. Main comparative analysis for primary and secondary outcomes will be performed using an intention-to-treat approach. To address missing data, multiple imputation will be performed as a sensitivity analysis. The significance level will be set at 0.05.

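### The main analysis is labelled intention-to-treat, but the mixed ANOVA named for it, as classically run, leaves out anyone with a missed visit, and imputation is only a sensitivity analysis

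*Protocol article*

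**What the plan says.** All the key statements stand in the Statistical analysis section of the protocol article.

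- Software: "SPSS version 17.0 or higher will be used for statistical analysis".
- Model: "Two-way mixed ANOVA will be used to determine within-subject and between subject variables".
- A second comparison: "Differences in mean change (baseline minus follow-up) will be compared between groups using baseline values of the outcomes as covariates".
- Analysis label: "Main comparative analysis for primary and secondary outcomes will be performed using an intention-to-treat approach".
- Missing data: "To address missing data, multiple imputation will be performed as a sensitivity analysis".

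No other handling of missing values is given for the main analysis.

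Two other places bear on this. The Methods paragraph of the abstract sets five assessments: "Assessment will be measured at baseline, immediately after treatment and at 3, 6, 12 month-follow ups". The Sample size section states the expected loss, "To allow for 20% drop out rate, a total sample size of 168 participants (42 per group) will be recruited", against 35 required per group. It also says that the estimates used repeated measure ANOVA.

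**The concern.** The label and the method do not fit together. Intention-to-treat means that participants are analysed as randomised and not selected by whether they came to every visit. A classical repeated-measures ANOVA takes one row per participant with one column per assessment, here five. A blank in any column removes the row. With imputation placed in the sensitivity tier, nothing in the stated main analysis brings those participants back.

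Two things are at stake. First, data already collected are thrown away: someone who attends up to 6 months and misses 12 months has four of five assessments recorded, and none would count. Second, randomisation protects the comparison of everyone randomised, not of those with full attendance. Table 2 gives treatment times of 30 minutes for local treatment alone, 45 for each single addition and 60 for the combination, and every arm practises its prescribed exercises daily at home. Drop-out could therefore differ by arm. That makes bias a plausible risk; the documents do not show that it will occur.

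**Working it through.** **1. The plan's own figures.** 35 × 1.20 = 42 per group, and 4 × 42 = 168. This reproduces the stated total from the stated 35. Adding 20% to the required number is not the same as keeping that number after a 20% loss: 35 / 0.80 = 43.75, or 44 per group and 176 in total.

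**2. Complete rows at the stated drop-out.** 168 × 0.80 = 134.4, about 134 participants. Per group, 42 × 0.80 = 33.6, below 35. Excluded: 168 − 134 = 34. This assumes that 20% are lost by 12 months and that nobody else misses a visit.

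**3. Adding intermittent gaps (assumed rates).** With independent misses at each of the three earlier follow-ups:

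- 3% per visit: 168 × 0.80 × 0.97³ = 123 complete rows (about 31 per group).
- 5% per visit: 168 × 0.80 × 0.95³ = 115 (about 29 per group).

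If instead all missingness is intermittent and independent over four follow-ups, complete rows are 168 × (1 − p)⁴:

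| Missed per visit (assumed) | Complete rows of 168 |
|---|---|
| 5% | 137 |
| 10% | 110 |
| 15% | 88 |
| 20% | 69 |

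**4. The change comparison by visit.** If participants who leave do not return, the 12-month comparison has the same 134. Earlier visits have between 134 and 168, depending on when people leave. With 5% intermittent misses, each visit keeps 168 × 0.95 = 160 instead of 137. This loses less, but each visit still includes only those who attended it.

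**5. Power.** The stated differences give standardised effects of 21.9 / 12.3 = 1.78 for sway and 4.5 / 3.2 = 1.41 for joint position error. For a two-group comparison with 33 per group, power is Φ(d√(n/2) − 1.96). For joint position error: 1.406 × √16.5 = 5.71, and Φ(5.71 − 1.96) = Φ(3.75), above 99.9%. Sway is higher still. At the plan's own effects, falling below 35 does not threaten power.

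**6. Possible bias (hypothetical).** A simulation took SD 3.2°, equal correlation of 0.3 to 0.7 between assessments, no true effect, and about 20% loss after the post-treatment visit. It compared the baseline-adjusted difference among participants with complete data.

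| Drop-out mechanism (assumed) | Bias post-treatment | Bias at 12 months | 12 months after imputing from observed values |
|---|---|---|---|
| Depends on post-treatment score in one arm only | 0.32° to 0.56° | 0.14° to 0.16° | about 0 |
| Depends on it equally in both arms | about 0 | about 0 | about 0 |

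In the first row the post-treatment bias comes entirely from discarding post-treatment values that had been recorded. The simulation covers baseline-adjusted analysis of completers, not the mixed ANOVA itself, so it shows the mechanism and does not forecast this trial.

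**The case against.** The strongest reply is that the article never says participants with a missed visit are dropped. That is correct. Exclusion is inferred from the method, and it would not follow if mixed ANOVA were loose wording for a likelihood-based linear mixed model. Nothing in the article points that way, however, and the Sample size section also speaks of repeated measure ANOVA, so the classical reading is the natural one.

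The second reply is that the baseline-adjusted change comparison, run by visit, would not lose a participant everywhere because of one gap. This also stands, and it limits the point: whole-row exclusion applies to the mixed ANOVA and not necessarily to every planned analysis. It does not rescue the label, since people absent at a visit are still absent from that comparison.

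Third, multiple imputation is already planned, and detail may sit in a full analysis plan. A robustness check is indeed there. But the article does not leave the ranking open: it states that imputation is the sensitivity analysis.

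A reader might also infer from the Postural stability section, "Participants are allowed a maximum of two additional attempts if they are unable to maintain the position for 30s", that a sway test failed on every attempt gives no score, so that the least stable participants go missing. The article does not say how such a test is scored, so that inference is unsupported and forms no part of this point.

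**Conclusion.** The point holds as a mismatch between the stated label and the stated method. On the natural reading, the primary analysis covers about 134 of 168 participants at the plan's own 20% drop-out, fewer if visits are also missed intermittently, and leaves unused the earlier data of about 34. This rests on the ANOVA being run in its classical form.

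Two stronger conclusions are tempting and should not be drawn. One is that the primary result will be biased. Bias in the comparison between arms needs drop-out to be related to scores differently by arm. Nothing in the documents establishes that, and neither size nor direction can be derived from them. The other is that the trial becomes underpowered because 33.6 falls below 35; at the stated effect sizes it does not. What is at issue is the validity of the headline comparison and the accuracy of its intention-to-treat label.

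**What to change.** Name as the primary analysis a likelihood-based linear mixed model for repeated measures, available as MIXED in SPSS. Include every randomised participant with at least one follow-up value, in the group assigned. Use baseline as covariate, with the two factors (sensorimotor exercise and balance exercise), time, and their interactions. Alternatively, make multiple imputation the primary analysis, which would use all 168. State in either case who enters the main analysis.

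Both options rely on drop-out being explained by observed values. Keep imputation under other missing-data assumptions as the sensitivity analysis, for example with imputed values shifted against the added exercise. Under the mixed model, this also covers participants with no follow-up at all.

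The cost is a change of wording and a little more analysis work, with the same software and the same data. It should be settled before anyone sees results by arm.

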## Discussion

Neck pain is a common health problem and is, along with low back pain, the world’s leading cause of years lived with disability [56]. To be effective, treatment must address not only the symptoms but also the impairments associated with neck pain. An effective treatment will help improve chances of a full recovery and prevent a recurrence of neck pain. This trial is the first to combine local neck treatment (manual therapy/therapeutic exercise) and specific approaches that target sensorimotor control and balance. The outcome of this trial will significantly facilitate informed decision making for the prevention and management of chronic neck pain.

This trial will investigate the effects of local neck treatment with and without tailored sensorimotor and balance exercise programs. The strengths of the study design are the pragmatic nature of treatment delivery towards clinical physiotherapy practices. Additionally, the exercise programs are individualized according to ongoing progress monitoring. It is expected that the findings of this trial will lead to improved clinical practice guidelines for persons with neck pain with impaired joint position sense and balance.

## Abbreviations

ANOVA: Analysis of variance
APmax: Maximum anterior-posterior
BPPV: Benign paroxysmal positional vertigo
CCF: Craniocervical flexor
CONSORT: Consolidated standards of reporting trials
CROM: Cervical range of motion
ICCs: Intraclass correlation coefficients
JPE: Joint position error
JPS: Joint position sense
MLmax: Maximum medial-lateral
NDI-TH: Neck disability index-Thai version
NRS: Numerical rating scales
PFSF: Patient-specific functional scale
SD: Standard deviation
SPSS: Statistical package for the social sciences
Thai SF-36: Thai version of short form 36
USA: United States of America
VAS: Visual analogue scale
